## Abstract

**Background:**

Parkinson’s disease progressively limits patients at different levels and as a result family members play a key role in their care. However, studies show lack of an integrative approach in Primary Care to respond to the difficulties and psychosocial changes experienced by them. The aim of this study is to evaluate the effects of a multidisciplinary psychoeducational intervention focusing on improving coping skills, the psychosocial adjustment to Parkinson’s disease and the quality of life in patients and family carers in a Primary Care setting.

**Methods:**

This quasi-experimental study with control group and mixed methods was designed to evaluate a multidisciplinary psychoeducational intervention. Based on the study power calculations, 100 people with Parkinson’s disease and 100 family carers will be recruited and assigned to two groups. The intervention group will receive the ReNACE psychoeducational intervention. The control group will be given a general educational programme. The study will be carried out in six community-based health centres. The results obtained from the two groups will be collected for evaluation at three time points: at baseline, immediately after the intervention and at 6 months post-intervention. The results will be measured with these instruments: the Quality of Life Scale PDQ-39 for patients and the Scale of Quality of Life of Care-givers SQLC for family carers, and for all participants the Psychosocial Adjustment to Illness scale and the Brief COPE Inventory. Focus groups will be organised with some patients and family carers who will have received the ReNACE psychoeducational intervention and also with the healthcare professionals involved in its development.

**Discussion:**

An important gap exists in the knowledge and application of interventions with a psychosocial approach for people with PD and family carers as a whole. This study will promote this comprehensive approach in Primary Care, which will clearly contribute in the existing knowledge and could reduce the burden of PD for patients and family carers, and also in other long-term conditions.

**Trial registration:**

NCT03129425 (ClinicalTrials.gov). Retrospectively registered on April 26, 2017.

## Background

Parkinson’s disease (PD) is a neurodegenerative disease which affects about 10 million people worldwide [1–3], and which currently has no cure. Numerous studies have been published which show the difficulties and psychosocial changes experienced by people with PD in their lives [4–8]. Similarly, recent research has highlighted that family members caring for people with PD also feel an important impact on their well-being and quality of life [9–11], as they are the patients’ main allies in order for them to carry on the activities of daily life. However, the limited and non-comprehensive approach that is offered to patients with PD and their family carers from Primary Care appears to be insufficient to encourage them to adapt to the changes that they experience as a consequence of this long-term condition (LTC) [12–15]. According to evidence, gender, education, coping, social networks or culture, are social and personal factors that can facilitate or hinder the psychosocial adjustment [16, 17]. In particular, coping has been identified as an essential factor in the improvement of the psychosocial adjustment to different LTCs [16, 17] and also to PD [11, 18]. This is because coping could help the patient with PD and the family carer in their search for balance in their lives [4, 14]. And also due to the psychosocial adaptation to PD is in turn a key mechanism for achieving better outcomes in terms of quality of life of patients with PD and their family carers [11, 18]. At present, few interventions [19, 20] have been found in the literature that aimed to improve coping skills and the psychosocial adjustment to PD. However, surprisingly changes in the development of coping skills and the psychosocial adjustment to PD were not directly measured in those studies [19, 20]. In addition, there is scarce number of psychoeducational interventions [20] that have taken into account needs from dyads, patients with PD and their family carers. Nevertheless, the influence that PD may have on the family carer’s wellbeing [9–11] cannot be neglected by healthcare professionals. To deal with this challenge in clinical practice, it is essential to develop and evaluate psychoeducational interventions which would help to counsel and motivate people with PD and their family carers in the adoption of coping skills which would lead to a better psychosocial adjustment to PD.

## Methods

### Aim

The aim of this present study is to improve the quality of life of people with PD and their family carers by means of a multidisciplinary psychoeducational intervention focusing on fostering coping strategies and their psychosocial adjustment to PD. The study also seeks to compare the effectiveness of the psychoeducational intervention focusing on the acquisition of coping skills with a control group receiving a general educational programme. The study will evaluate the perceptions, opinions and satisfaction of the patients and family carers who receive the psychoeducational intervention and will explore the reflections of the social and healthcare providers involved in this intervention.

On the basis of previous research [9–14, 18], the hypothesis we propose is that through the development of coping skills which will contribute to promoting a positive psychosocial adjustment to PD, the quality of life of the people with PD and their family carers will be improved. And the second hypothesis we suggest is that this psychoeducational intervention will enhance the quality of life of the patients and family carers more than a general education programme.

If we find significant results in this psychoeducational approach, we consider that at the long-term, this could develop larger scale interventions and have positive effects on the overall health of patients and their family carers. In particular, we expect that, by integrating psychoeducational interventions into care pathways, the patients and family carers will perceive a greater sense of normality in their lives [4, 10, 12, 21], which will also promote compliance with drug treatments and healthy lifestyles and professionals would be able to identify and support cases with poor illness management and coordinate levels of care more efficiently.

### Design

The study design will be quasi-experimental with a control group, repeated measures and a combination of quantitative and qualitative methods. Figure 1 shows a schematic outline of the study design and Table 1 presents the project timeline. The baseline recruitment of participants and data collection started in March 2015 and is still ongoing (30% of the study still to be completed by the end of 2018).

**Fig. 1 Fig1:**
[figure not shown]
Flow diagram with the design of this study. PD: Parkinson’s Disease

**Table 1 Tab1:** Project Timeline

	Year 1 (2015)			Year 2 (2016)			Year 3 (2017)			Year 4 (2018)		
Task	Q1	Q2	Q3	Q4	Q5	Q6	Q7	Q8	Q9	Q10	Q11	Q12
Random allocation of interventions to participating centres	×											
Dissemination of interventions in participating centres	×	×	×	×	×	×	×	×	×			
Delivery of letters to patients and carers	×		×		×		×		×			
Data collection at baseline (Questionnaire T0)	×		×		×		×		×			
Participants from experimental and control groups receive the intervention at a time	×		×		×		×		×			
Data collection after the intervention (Questionnaire T1)	×		×		×		×		×			
Data collection 6 months post-intervention (Questionnaire T2)			×		×		×		×		×	
Focus groups post-intervention with patients and carers					×	×	×					
Focus group with professionals										×		
Analysis of qualitative data					×	×	×	×	×	×	×	×
Analysis of quantitative data											×	×
Dissemination of findings											×	×

This study is part of the ReNACE research programme aimed at designing multidisciplinary and individualised interventions to promote positive living with a LTC in patients and relatives.

### Setting

The study will be carried out in several urban areas of Navarra, in the North of Spain. Specifically, the six health centres in a community setting with the largest numbers of people diagnosed with PD will be chosen in order to maximise the recruitment of participants and improve the power of the study. At the end of the recruitment of participants, ANOVA and χ^2^ tests will be performed to explore the sociodemographic characteristics of the participants from the intervention group and the control group. In the case of finding a significant difference in a sociodemographic variable, the statistics analyses will adjust by propensity-score analysis or the most suitable statistical technique.

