### Participants

Participants will be people with PD receiving care as outpatients in the designated centres, over the age of 18 years, in any stage of the disease (as determined by a researcher with the Hoehn & Yahr scale [22]), residing at that time in Navarra, fluent in the speaking and understanding of the Spanish language, and with preserved cognitive ability (as determined by medical history or the doctor responsible).

Family members/carers will be over the age of 18, living or maintaining a close relationship with the patient and actively collaborating in his/her care, currently residing in Navarra and fluent in the speaking and understanding of the Spanish language.

Individuals with PD may enter the research project even though they do not have a family carer or the carer does not wish to participate. The family carer will also be able to enter the research project even though the individual with PD cannot participate for not meeting the inclusion criteria or for lack of interest.

Any change in participants’ circumstances during the study which mean that they do not meet the inclusion criteria mentioned above will cause the discontinuation of the participants in the study.

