### Outcome measures

#### Quantitative data collection

The primary outcome is the improvement in quality of life of the people with PD and of the family carers participating in the ReNACE psychoeducational intervention, in comparison with the change observed in the quality of life of those participating in the general educational programme. The secondary outcomes will be the changes in the coping skills and in the psychosocial adjustment to PD. These outcomes will be measured in the control and intervention groups at 3 time points; baseline (T0); immediately after the end of the intervention (T1); and 6 months post-intervention (T2). To ensure blinding of the groups and the intervention, researchers involved in data collection will not have participated in any of the group sessions and known the group allocation. At baseline (T0) the sociodemographic data of the participants will be collected. At the three time points the following instruments will be used to measure the outcomes:

Patients:The Quality of Life Scale in Parkinson’s disease (PDQ-39) [29, 30]The Psychosocial Adjustment to Illness scale (PAIS-SR) [31]The Brief COPE scale [32, 33]

Family carers:The Scale of Quality of Life of Care-givers (SQLC) [23, 34]The Psychosocial Adjustment to Illness scale (PAIS-SR) [31]The Brief COPE scale [32, 33]

The measurement scales selected are validated instruments which furthermore, have been used previously in a study of the ReNACE programme in PD patients and their family carers [11].

It is calculated that the participants will need approximately 1 hour to complete the questionnaires. When the participants finish the questionnaire, the researcher will check that they have been filled in correctly in order to minimise data loss.

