### Data analysis

#### Quantitative data

Analysis of quantitative data will be performed on an intention to treat basis and for that SPSS version 23.0 will be used. A descriptive analysis of the sociodemographic data will be made. For the quantitative variables, means and standard deviations will be calculated. Mixed ANOVA within-pairs and between-pairs to compare patients with family carers at each measurement points, unpaired student t tests to determine any significant differences between the two groups at baseline (T0) and the measurements at T1 and T2 will be used. Also, a mixed factorial ANOVA with 1 between-subjects factor with 2 levels (intervention and control), and 1 within-subjects factor with 3 levels (baseline, time 1 post-intervention, time 2 post-intervention) will be used to compare differences between the two groups in the main variables over time. If any demographic variable result different will be use as a covariate in this analysis.

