### Limitations

The non-randomised and voluntary nature of the participation could limit the generalisation of results. However, statistical generalization is not sought in this study but a breakthrough in an area of interventional research that has been neglected for many years when it comes to PD and family carers and illness adjustment. In particular, patients at an advanced stage of PD may not take part in the intervention due to their disability and that young patients who have been diagnosed only recently may not enroll in the intervention due to the stigma of PD being thought of as a disease of the elderly. However, given that centres from different health areas of Navarra will participate, it is expected that the likelihood of this effect influencing the results will be diminished. Similarly, the reliability and sensitivity of the measurement scales that will be used in the study, together with the use of repeated measures, the presence of a control group and the baseline comparison between groups, are all important factors that will help to overcome the limitation mentioned above.

Another limitation could be the baseline differences between the centres selected in the quasi-experiment. However, it is expected that non-statistically significant differences will be found between participants given that the populations of the centres share a similar socio-economic and cultural context.

Furthermore, a limitation of this study is to successfully encourage people with PD and their family carers, who generally do not participate in activities on a regular basis, to attend the intervention each week. It is necessary to bear in mind that given the age and physical condition of the target population the number of subjects lost to the study could be greater than usual in longitudinal studies. However, to minimise this effect, at the end of each session participants will receive a small introduction to the topic of the following week which will help to increase enthusiasm and promote regular attendance.

It is also necessary to point out that in this study it is not possible for the professionals giving the sessions to be blinded, given that there are two different types of intervention. However, researchers involved in the data collection and participants for group A and B will be blinded to the intervention. Also the content and methodology of each session will be established previously in a manual that the professionals will use.

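### Covariate adjustment depends on a significant baseline test of sociodemographic variables, which misses sizeable imbalances at 52 per arm and which disease stage cannot trigger

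*Protocol article*

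**What the plan says.** The rule appears twice in the protocol article.

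- **Setting.** Once recruitment ends, ANOVA and chi-square "tests will be performed to explore the sociodemographic characteristics of the participants from the intervention group and the control group". No significance level is given. Whether anything is adjusted then hinges on "finding a significant difference in a sociodemographic variable, the statistics analyses will adjust by propensity-score analysis or the most suitable statistical technique".
- **Data analysis, Quantitative data.** After describing the mixed factorial ANOVA (two groups by T0, T1, T2), the text adds: "If any demographic variable result different will be use as a covariate in this analysis". It does not say what counts as different. Read with Setting, it is the significance test. The same paragraph plans "unpaired student t tests to determine any significant differences between the two groups at baseline (T0) and the measurements at T1 and T2", with no adjustment following from the T0 result.

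Three other places bear on the rule.

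- **Participants** admits patients at any stage of disease, "as determined by a researcher with the Hoehn & Yahr scale". Stage appears in neither adjustment rule.
- **Procedure** allocates by centre, with six centres and a coin toss.
- **Limitations** names baseline differences between centres as a weakness and replies that "it is expected that non-statistically significant differences will be found between participants".

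**The concern.** A baseline significance test answers the wrong question. Whether a variable confounds depends on how far the arms differ on it and how strongly it predicts the outcome. The p-value reflects the first only through the sample size and the second not at all. In a small study, an imbalance large enough to matter will often pass as non-significant and go unadjusted.

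The design makes this more than a formality. With six centres and no individual randomisation, adjustment is one of the main safeguards. Yet the screen covers sociodemographic variables only. Disease stage, an obvious prognostic factor for quality of life in Parkinson's disease, lies outside it. The wording in Setting also leaves the technique to be decided once the baseline differences are known.

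**Working it through.** **Inputs.** From Table 2 and the Sample size section: 52 patients and 53 carers per group; PDQ-39 SD 15.44; target difference 10 points; power 80%; losses 25% for patients. For carers: SD 25.04, difference 15, losses 20%. Assumed because the article does not state them: two-sided alpha 0.05, independent participants, the correlation between covariate and outcome, and the number of variables screened.

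**The plan's own figure.** n = 2[SD(1.96 + 0.84)/difference]².
- Patients: 37.4 from the normal formula, 39 with the t distribution; 39/0.75 = 52, as stated.
- Carers: 43.7, so 44; 44 × 1.20 = 52.8, so 53 as stated (44/0.80 would give 55).

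The two-sided 5% assumption therefore fits. A one-sided test gives 40 and 44 and does not. The sample size is not affected by this point.

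**Sensitivity of the trigger.** The power of a two-sample t test at 52 per arm, for a true imbalance of d SD, has noncentrality d√(52/2) = 5.10d.

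| True imbalance | Chance of being flagged |
|---|---|
| 0.2 SD | 17% |
| 0.3 SD | 33% |
| 0.4 SD | 52% |

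Reaching 80% takes about 0.55 SD. For a binary variable, 50% against 65% is flagged 34% of the time.

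**What passes as non-significant.** The largest observed difference that stays non-significant is about 1.96 × √(2/52) = 0.38 SD. The bias it carries into a single-time comparison is imbalance × correlation × SD:
- correlation 0.3: 0.38 × 0.3 × 15.44 = 1.8 points
- correlation 0.5: 0.38 × 0.5 × 15.44 = 2.9 points

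That is 18% to 29% of the 10-point target.

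**Three strategies compared.** Simulation with 20,000 runs, 52 per arm with no losses, no treatment effect, correlation 0.5, one post-intervention comparison. Each cell gives mean bias in PDQ-39 points, with type I error in brackets.

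| True imbalance | Never adjusted (as for stage) | Adjusted only if significant | Always adjusted |
|---|---|---|---|
| 0.2 SD | 1.5 (7.8%) | 0.9 (5.1%) | 0.0 (5.2%) |
| 0.3 SD | 2.3 (11.4%) | 1.0 (5.7%) | 0.0 (5.0%) |
| 0.4 SD | 3.1 (17.3%) | 0.9 (6.1%) | 0.0 (4.9%) |

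**Where the bias lands.** Let a covariate with imbalance d shift the outcome by b₀d at T0 and b₁d at T1. The T1 comparison is biased by b₁d. The change from T0, which the group-by-time term tests, is biased by (b₁ − b₀)d. That is zero if the covariate acts equally at all times, and not zero if it affects the course.

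**False flags.** With no true imbalance and k independent variables screened, the chance of at least one flag is 1 − 0.95^k: 23% for k = 5, 34% for k = 8, 40% for k = 10. If centres differ, tests that ignore centre flag more often per variable: about 7% at ICC 0.01 and 15% at ICC 0.05 (assumed ICCs, six centres of 17, three per arm).

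**The case against.** Several stronger readings are tempting, and the document does not support them.

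- *The two sections contradict each other on method.* They need not. The open clause in Setting can include the covariate method named in Data analysis. The fair criticism is that the method is left open.
- *The baseline outcome is ignored.* It is not. T0 is one of the three levels of the mixed ANOVA, and the primary outcome is framed as change. Confounding that is constant over time drops out of the group-by-time term. The unadjusted T1 and T2 t tests, and confounding of the course, are not protected.
- *Most confounding stays unadjusted.* Not for screened variables. In the simulation the rule removes about 43%, 56% and 71% of the bias at 0.2, 0.3 and 0.4 SD, and type I error stays between 5.1% and 6.1%. The large errors belong to a variable that is never screened.
- *The method is picked with outcomes in view.* The trigger uses sociodemographic data at the end of recruitment. Table 1 puts the last baseline wave in Q9 and the start of quantitative analysis in Q11. What the rule exposes is baseline data.
- *Adjusting for chance differences biases the result.* It does not. It costs prespecification only.
- *Stage can never enter the model.* It cannot trigger adjustment. If another variable does, a propensity model could include it, though nothing says so.
- *Limitations proves that non-significance will be taken as balance.* That sentence states an expectation, not an analysis rule.

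A condensed article may also leave the covariate list to an analysis plan. That is so, and the missing list is not the complaint. The stated trigger is, and a plan that followed it would inherit it.

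**Conclusion.** The concern holds in a limited form. The protocol fixes an adjustment rule that responds to p-values on sociodemographic variables only. At 52 per arm it misses a 0.3 SD imbalance about two times in three and a 0.4 SD imbalance about half the time, and disease stage cannot set it off. For screened variables the residual bias is modest, about 1 PDQ-39 point on average in the simulation. For an unscreened prognostic variable it is 1.5 to 3.1 points, with type I error of 8% to 17%.

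These bias figures assume a correlation of 0.5 and independent participants, and they apply to the T1 and T2 comparisons. For the group-by-time test, only confounding that changes over time remains. The power figures rest on two-sided 0.05 and independence, which allocation by centre puts in doubt. The rule should be changed, but it does not by itself invalidate the main analysis.

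**What to change.** In both Setting and Data analysis, replace the significance trigger with one covariate set, named in advance and used whatever the baseline differences.

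- **Patients:** Hoehn & Yahr stage, age, sex, and any other prognostic sociodemographic factor chosen beforehand. Education is a candidate, since the Background lists it among the factors that help or hinder adjustment.
- **Carers:** age, sex, and the same type of factor.
- **Model:** include covariate-by-time terms in the repeated-measures analysis, so that effects on the course are adjusted for as well as effects on the level. Use the same set for the T1 and T2 comparisons.
- **Baseline outcome:** either a covariate with only T1 and T2 as responses, or the T0 response level as now. Not both, since T0 would then be response and predictor at once.
- **Method and reporting:** drop the open choice of technique and the baseline tests; describe baseline characteristics by arm and by centre.

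The cost is minor rewording and a few degrees of freedom. No new assessment is needed: stage is determined at entry, and the scales and sociodemographic data are collected at T0 ("At baseline (T0) the sociodemographic data of the participants will be collected"). The sponsor should confirm that the stage value is kept in the analysis data. Individual covariates do not deal with clustering by centre, which needs its own treatment.
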